## METHODOLOGY

### Investigational drug

Metformin (*Metforal* 850 mg, Registration No. 00-1081, Anatomical Therapeutic Chemical (ATC) code A10BA02) is an oral antidiabetic drug with antihyperglycemic activity. *Metforal* 850 mg contains the active substance metformin. It belongs to a group of medicines called biguanides for the treatment of type 2 diabetes mellitus (non-insulin-dependent diabetes) in adults and in children of 10 years of age or in children and adolescents above 10 years. Metformin is a dimethylbiguanide that lowers both basal and postprandial plasma glucose levels. It is used when diet therapy and exercise do not provide adequate glycemic control (summary of drug characteristics, harmonized SAM of Latvia 30.06.2011). Metformin is recommended as a first-choice medicine to prevent hyperglycemia in patients with type 2 diabetes (T2D) [International Diabetes Federation Guideline Development Group, 2014; Inzucchi et al., 2015]. In addition, the drug may be used as a prophylactic agent in patients with impaired glucose tolerance in order to reduce their health status deterioration and the risk of developing diabetes mellitus [Canadian Diabetes Association Clinical Practice Guidelines Expert Committee, 2013; Hostalek et al., 2015; Inzucchi et al., 2015]. The benefits of metformin therapy are: high safety profile (low risk of hypoglycemia (0-21%) compared to other oral antidiabetic medication products), high efficacy, neutrality or lowering effect on body weight and cardioprotective effects [Bolen et al., 2007; Fung et al., 2015; Inzucchi et al., 2015].

Three antihyperglycemic mechanisms of action have been observed for metformin: suppression of gluconeogenesis and glycogenolysis, improvement of peripheral glucose uptake and use, inhibition of absorption of glucose in the intestine (summary of drug characteristics, harmonized SAM of Latvia 30.06.2011). Adenosine monophosphate activated protein kinase (AMPK) is considered to be the dominant mechanism underlying metformin action at the molecular level [Zhou et al., 2001; Musi et al., 2002; Diamanti-Kandarakis et al., 2010]. AMPK, the cell's energy sensor, is involved in many metabolic processes by regulating enzymes that provide gluconeogenesis, lipid synthesis and oxidation [Lan et al., 2008; Canto et al., 2009; Cao et al., 2014]. AMPK stimulates translocation of the glucose transporter 4 (GLUT4) to cell membranes, partly explaining higher uptake of glucose in tissues in the presence of metformin (Lee et al., 2012). Functional mechanisms of the drug also cover the activation of classic insulin signaling pathway (IRS/PI3K/Akt) [Xu et al., 2016]. Inhibition of mitochondrial complex I changes the ATP/AMP ratio and secondary activates AMPK, reduces the activity of mitochondrial glycerophosphate dehydrogenase (mGPD), which blocks glucose synthesis from glycerol [Andrzejewski et al., 2014; Madiraju et al., 2014; Hur and Lee, 2015].

The bioavailability of orally taken metformin ranges from 50 to 60%. The medication is absorbed in the small intestine and further directed through circulation to target organs, with the highest concentration reached in the liver (3-5 times higher than in the gate vein). Metformin is not metabolized in the body and is extracted unchanged through the kidneys [Graham et al., 2011; McCreight et al., 2016]. After an oral dose intake, 20-30% is not absorbed and is excreted in the feces. The liver is considered to be the primary target organ of metformin and its glucose lowering

effect is mainly due to the reduction of gluconeogenesis in hepatocytes [Hundal et al., 2000]. Other effects include the promotion of glucose uptake, inhibition of lipogenesis and activation of fatty acid oxidation in the liver, muscle and adipose tissues, and inhibition of lipolysis in adipose tissues [Diamanti-Kandarakis et al., 2010].

### **Dosage, packaging, storage of the investigational drug**

Each study participant will take 850 mg of metformin twice a day (10 to 12-hour interval) for a week. During the study, the therapeutic daily dose of the drug (1700 - 2250 mg) will not be exceeded. Participants will use the medication during or after eating with a glass of water to reduce the risk of side effects. Each study participant will receive a package of 14 *Metforal* 850 mg tablets during their 3rd visit. Participants will be instructed on the dosage, regimen, duration and possible side effects of the medication. According to the manufacturer's instructions, the product does not require any special storage conditions. The drug will be delivered to the research participant in its original package - PVC / Aluminum plate.

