#### 2. Use of investigational drug

Only the volunteers whose biochemical analysis and the information filled in the general questionnaire still indicate on a compliance with the inclusion / exclusion criteria will continue to participate in the study. The study participants will use film-coated tablets of *Metformal* 850 mg twice daily (within the interval of 10 to 12 hours) for 7 days. In parallel, participants will be asked: (1) to document their nutrition in a previously issued diet diary on a regular basis, (2) to collect stool samples independently at home and (3) to donate blood samples on their scheduled visits.

During the study, participants will be asked to refrain from drastic lifestyle alterations and dietary changes, except for the activities required for the study.

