***3rd visit - Study Day 4.*** Blood samples (7 - 13 ml) will be collected from the participant's at fasting-state for further genotyping, DNA methylation, RNA expression and metabolite analysis. Participants will deliver a filled general questionnaire previously collected stool samples. The investigator will provide each participant with 14 film-coated *Metforal* 850 mg tablets and re-instruct on the mode of administration, duration, dose, storage and return of the drug. The administration of *Metforal* 850 mg will begin.

**4th visit - Study Day 4.** 10 hours after the first dose of the *Metformal* 850 mg (before the second dose), blood samples (7 - 13 ml) from the study participant will be repeatedly collected for DNA methylation, RNA expression and metabolite analysis. Participants will be instructed to collect the second stool sample on day 5 of the study.

**5th visit - Study Day 6.** Participants will be asked to attend a control visit in order to obtain the information about the participant's well-being and evaluate their compliance with the study protocol. Participants will bring the stool samples collected on Day 5.

**6th visit - Study Day 11** (the day after the last intake of *Metformal* 850mg). Blood samples at fasting-state will be obtained for DNA methylation, RNA expression and metabolite analysis. If necessary, the participant will return the unused *Metformal* 850 mg tablets. Participants will be asked to collect a stool sample within this day.

**7th visit - Study Day 12,** The final inspection visit. Participants will bring the stool samples collected on Day 11, filled diet diaries and questionnaire on side effects. The participant of the study will be informed about the upcoming telephone call on the 13th day of the study.

**Phone call visit - Study Day 13.** The investigator will contact each participant by phone, making sure about the participant's well-being and any side effects observed. If necessary consultation of physician or other certified specialist will be recommended. The investigator will answer any question regarding the progress of the study and inform the participants about the end of the active participation in the study.

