### **DNA and RNA analysis**

Genomic DNA from venous blood samples will be extracted according to a standard phenol-chloroform extraction technique in a LGDB laboratory. RNA isolation will be done with commercially available reagent kits such as the 5Prime PerfectPure RNA Blood Kit, following the manufacturer's instructions. DNA and RNA samples will be stored at -70 ° C in the LGDB premises.

The DNA extracted from blood samples (obtained in the 3rd visit) will be further used for genotyping in order to identify the polymorphisms so far associated with metformin tolerance, which will facilitate the selection of participants who are genetically predisposed to experience adverse reactions during metformin use. The genetic analysis will provide more information about the genetic factors of the host potentially affecting the gene expression profiles, composition of the gut microorganisms and their functions.

In addition, metformin-induced changes in the epigenetic gene regulation, DNA methylation and gene expression profiles, will be determined by comparing reference samples (collected before taking the first metformin dose on visit 3) with samples obtained after the first dose of *Metforal* 850 mg (10 h after the first metformin dose, visit 4) and samples collected at the end of *Metforal* 850 mg treatment for 7 days (visit 7). DNA methylation analysis will be adjusted by neutrophil/leukocyte ratio, which will be calculated using hematological parameters. Measurements of metformin concentration in plasma will be used as an additional factor in DNA methylation analysis. The functionality of the alterations identified in the DNA methylation analysis will be confirmed based on the correlation between the DNA methylation profiles and RNA expression level at specific loci. An association between DNA methylated profiles, transcriptome profiles and metformin tolerance indicators will be analyzed. These findings will provide information on the molecular mechanisms underlying the multiple therapeutic directions of metformin.

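### The end-of-treatment methylation and RNA blood sample is tied to visit 7 in one section and to Day 11 (visit 6) elsewhere, and nothing records the hours since the last dose

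*Protocol*

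**What the plan says.** On dosing, the Protocol section on dosage, packaging and storage states: "Each study participant will take 850 mg of metformin twice a day (10 to 12-hour interval) for a week". The description of the treatment period repeats it: "twice daily (within the interval of 10 to 12 hours) for 7 days". Fourteen tablets are handed out at visit 3. The administration section says that no doctor or investigator directly supervises intake and that compliance is checked at visits.

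On sampling after the first dose, the visit 4 entry is specific. Blood is taken 10 hours after the first tablet, and "before the second dose), blood samples (7 - 13 ml) from the study participant will be repeatedly collected".

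On end-of-treatment blood, the visit 6 entry (Day 11, the day after the last tablet) says: "Blood samples at fasting-state will be obtained for DNA methylation, RNA expression and metabolite analysis". It gives a day and a fasting condition, but no clock time and no number of hours from the last dose. The DNA and RNA analysis section, which defines the comparison of baseline, first-dose and end-of-treatment samples, instead identifies the last one by the words "850 mg treatment for 7 days (visit 7".

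That section also makes plasma metformin concentration an additional factor in the methylation analysis. The list of endpoints makes the association of pharmacokinetic parameters with taxa, methylation and expression a secondary endpoint.

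**The concern.** Two things are unsettled about the same blood sample.

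First, the section that defines the methylation and expression comparison names a visit at which the schedule takes no blood. Followed literally, it would move the sample a day further from the last tablet.

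Second, the time from the last tablet to the draw is neither set nor recorded. The Protocol says metformin is not metabolised and leaves the body unchanged through the kidneys, so once dosing stops the plasma level depends on how long ago the last tablet was taken. In an analysis that uses plasma level as an exposure variable, a participant with a low level may have low exposure or may simply have had a longer gap before the draw. Without dose times the two cannot be told apart, and times that were not written down cannot be recovered at the analysis stage.

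**Working it through.** **Where each section puts the end-of-treatment blood**

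| Protocol section | Placement |
|---|---|
| Figure 1 table | Day 11, fasting |
| Observational period, opening text | Day after the last dose |
| Visit 6 entry | Day 11, fasting, day after the last tablet |
| Blood sample collection | Day 11, 7 days after the first dose |
| DNA and RNA analysis | Visit 7 |
| Visit 7 entry | Day 12; stool samples, diaries and questionnaire handed in; no blood listed |

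Four places agree on Day 11 or its equivalent. One names visit 7.

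**The plan's own dosing figures**

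- Tablets: 2 per day × 7 days = 14, as dispensed.
- Daily dose: 2 × 850 mg = 1700 mg, within the stated limit.
- Last dosing day: first dose on Day 4, seven days of use, so Days 4 to 10. The follow-up section counts three days after the last intake within a 13-day total, and 13 − 3 = 10 agrees.

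**Hours from last dose to the draw**

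Assumptions: the 10 to 12 hours is the gap g between the two doses of one day; the morning dose is at the same clock time every day; blood is drawn at that clock time. The Protocol gives no hours, so these are mine.

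With the first dose at hour 0:

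- Last (14th) dose: 6 × 24 + g = 144 + g.
- Day 11 draw: 7 × 24 = 168, so hours since last dose = 168 − (144 + g) = 24 − g.
- Day 12 draw: 8 × 24 = 192, so hours since last dose = 192 − (144 + g) = 48 − g.

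| g (h) | Last dose (h) | Day 11 draw (h since dose) | Day 12 draw (h since dose) |
|---|---|---|---|
| 10 | 154 | 14 | 38 |
| 11 | 155 | 13 | 37 |
| 12 | 156 | 12 | 36 |

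On Day 11 the permitted interval alone gives a spread of 14 − 12 = 2 hours. Each hour by which the draw is later than the usual morning dosing time adds one hour. The visit-number conflict is worth 24 hours.

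**What the Protocol asks to be recorded**

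The table of anticipated problems has a skipped tablet noted in the diet diary. No section asks for the clock time of a tablet. The Protocol gives no elimination half-life, so I have not converted hours into a difference in concentration.

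**The case against.** The visit number is very probably a slip. The same sentence names visits 3 and 4 correctly, visit 7 has no draw, and every other section points to Day 11. Site staff following the schedule would draw on Day 11. This stands: the 36 to 38 hours is what a literal reading yields, not a forecast of what will happen.

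It can also be said that plasma metformin is measured directly, that a 2-hour spread is modest, that adjusting for hours since dose belongs to the analysis plan, and that the diary form is not shown and may already ask for times. Part of this stands. I make no finding from the absence of a covariate, and if the form already has a time field, one sentence in the Protocol is enough. But a measured level describes the moment of the draw. Comparing levels between people as exposure needs the time since dose, and that is a matter of data capture, which an analysis plan cannot repair.

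A reader might infer something stronger: that the dosing rule contradicts itself. Two intervals making up 24 hours can both lie within 10 to 12 hours only if each is 12. If every consecutive gap were shorter, three tablets (3 × 850 = 2550 mg) would fall within some 24-hour window, against "the therapeutic daily dose of the drug (1700 - 2250 mg) will not be exceeded". The documents do not support this. The rule says twice a day, and the visit 4 draw 10 hours after the first tablet and before the second fits an interval between the day's two doses. On that reading any gap from 10 to 12 hours agrees with 14 tablets, Days 4 to 10 and 1700 mg a day. The round-the-clock schedules are not compliant. Starting at 08:00 on Day 4 (assumed), a constant 10-hour gap puts three doses on Day 6 (00:00, 10:00, 20:00), and an 11-hour gap puts three on Day 8 (00:00, 11:00, 22:00). The larger spreads in time since last dose that such schedules would produce therefore do not describe people who follow the Protocol. Nor does anything show the 2250 mg figure to be wrong: the planned 1700 mg lies below it, and a ceiling need not be a multiple of the tablet strength.

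**Conclusion.** The point holds in two limited parts. The DNA and RNA analysis section contradicts the visit schedule on when the end-of-treatment blood is taken. This is close to clerical, but it sits in the section that defines the comparison and is worth 24 hours if followed. Separately, the Protocol neither fixes nor asks for the hours from last dose to that draw. Under the assumptions above, compliant participants differ by about 2 hours on Day 11, plus any variation in draw time, so part of the difference in plasma concentration will be timing. The effect on concentration cannot be sized from the Protocol.

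The primary endpoint, gut microbiome composition from stool, is not affected. The methylation and expression results and the pharmacokinetic associations are. The sections on dosing do not say whether the 10 to 12 hours also applies overnight. That is an ambiguity, not an arithmetic impossibility.

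**What to change.** - Reconcile the visit number in the DNA and RNA analysis section with the Figure 1 table, the observational-period text, the visit 6 entry and the blood collection section.
- Have participants note the clock time of their tablets in the diet diary they already keep, at least for the last tablet before the Day 11 draw, and record the time of the draw.
- Use hours since last dose when interpreting or adjusting plasma concentration in the end-of-treatment methylation analysis and the pharmacokinetic associations.
- Optionally, state in the two dosing passages which gap the interval describes. Which rule is right is for the sponsor and investigator to say.

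The cost is a wording amendment, one diary entry, one recorded time and one derived variable. The downside is slightly more recording by participants.

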### **Administration of investigational drug**

Participants of the study will orally use *Metforal* 850 mg coated tablets twice daily for 7 days. The use of the drug will take place without a direct supervision of a doctor or investigator, although the compliance with the protocol will be controlled within regular visits. 14 *Metforal* 850 mg tablets will be delivered to the participants in its original package by the investigator or his representative during the 3rd visit, the participants will receive instructions for the appropriate use of the investigational drug, the number of tablets delivered to participants as well as the date of delivery will be strictly documented.

### **Blood sample collection**

Within the framework of the study, venous blood samples (7 - 13ml) will be collected from participants (1) during the verification period, (2) immediately before the use of metformin, (3) 10 hours after the first dose of metformin, (4) 7 days since the beginning of metformin administration. During the verification period, the participant will donate a blood sample in any E. Gulbis laboratory (11 ml) for hematological and biochemical analysis. Blood samples for the analysis of DNA, RNA and metabolites will be collected on day 4 of the study (before and after the first dose of metformin) and on day 11 at LBMC. Venipuncture will be performed by a certified medical practitioner using appropriate equipment.

### **Hematological and biochemical analysis**

The hematological and biochemical analysis will be performed in a specialized laboratory in accordance with generally accepted standard procedures. The analysis will include the following measurements: total blood count, vitamins (vitamin B12, etc.), creatinine, HbA1c, plasma glucose, bile acid, total bilirubin, ALT, GGT, alkaline phosphatase, CRO, total cholesterol, non-ABL cholesterol, high / low density cholesterol and triglycerides, etc. The list of analysis to be

performed can be changed based on the results obtained and according to the direction of the research progress.

### **DNA and RNA analysis**

Genomic DNA from venous blood samples will be extracted according to a standard phenol-chloroform extraction technique in a LGDB laboratory. RNA isolation will be done with commercially available reagent kits such as the 5Prime PerfectPure RNA Blood Kit, following the manufacturer's instructions. DNA and RNA samples will be stored at -70 ° C in the LGDB premises.

The DNA extracted from blood samples (obtained in the 3rd visit) will be further used for genotyping in order to identify the polymorphisms so far associated with metformin tolerance, which will facilitate the selection of participants who are genetically predisposed to experience adverse reactions during metformin use. The genetic analysis will provide more information about the genetic factors of the host potentially affecting the gene expression profiles, composition of the gut microorganisms and their functions.

In addition, metformin-induced changes in the epigenetic gene regulation, DNA methylation and gene expression profiles, will be determined by comparing reference samples (collected before taking the first metformin dose on visit 3) with samples obtained after the first dose of *Metforal* 850 mg (10 h after the first metformin dose, visit 4) and samples collected at the end of *Metforal* 850 mg treatment for 7 days (visit 7). DNA methylation analysis will be adjusted by neutrophil/leukocyte ratio, which will be calculated using hematological parameters. Measurements of metformin concentration in plasma will be used as an additional factor in DNA methylation analysis. The functionality of the alterations identified in the DNA methylation analysis will be confirmed based on the correlation between the DNA methylation profiles and RNA expression level at specific loci. An association between DNA methylated profiles, transcriptome profiles and metformin tolerance indicators will be analyzed. These findings will provide information on the molecular mechanisms underlying the multiple therapeutic directions of metformin.

**Methods:** For global DNA methylation analysis bisulfite conversion will be performed (EZ DNA Methylation-Gold kit, Zymo Research). Next generation sequencing of bisulfite converted DNA (Illumina 450K Methylation Microchip, Illumina iScan system) is planned as an outsourcing at Uppsala University, Sweden. RNA-Seq will be performed using Low Input RiboMinus Eukaryote System v2, Ion Total RNA-Seq Kit v2 (Thermo Fisher Scientific) on Ion Proton sequencer, Ion PI Chip in LBMC. Genotyping as outsourcing will be done with Infinium Core-24 Kit, Illumina and Illumina iScan system.

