## **STUDY DESIGN**

The study is interventional and longitudinal; each participant serves as a control for itself. Advantages of longitudinal study: automatic control of constant influencing factors (participant's genotype, gender) and control of constant factors arose during the study period (participant's age, socioeconomic status, environment, etc.). The individual predisposition to a specific drug-induced response of the body, is taken into account [Gilbert et al., 2016; Petersen et al., 2016].

One of the main drawbacks for cross-sectional studies based on classical case / control design is the lower ability to distinguish between the causal relationship between associated factors [Gilbert et al., 2016]. In addition, the statistical power of cross-sectional studies is negatively

influenced by high variability of microbiome composition and epigenetic patterns among individuals [The Human Microbiome Project Consortium, 2012]. Prospective studies of interactions between metformin and gut microbiome taking into account the gut microbiome profile before the use of the drug, allowing more accurate judgment of its effects, have not been performed so far.

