|                                                                | 1                             | 2 | 3                                       | 4                                       | 5                       | 6 | 7 | 8 | 9 | 10 | 11                                      | 12 | 13         |
|                                                                | Verification period           |   |                                         | Use of investigational drug             |                         |   |   |   |   |    | Observational period                    |    |            |
|                                                                | Filling of diet diary         |   |                                         |                                         |                         |   |   |   |   |    |                                         |    |            |
|                                                                |                               |   | Blood samples collected (fasting state) | Blood samples collected (fasting state) | Stool samples collected |   |   |   |   |    | Blood samples collected (fasting state) |    | Phone call |
|                                                                |                               |   | Stool samples collected                 | Blood samples collected (after 10h)     |                         |   |   |   |   |    | Stool samples collected                 |    |            |
|                                                                |                               |   |                                         | Metformin twice a day/2x850mg           |                         |   |   |   |   |    |                                         |    |            |
|                                                                | General questionnaires filled |   |                                         |                                         |                         |   |   |   |   |    | Questionnaires of side effects filled   |    |            |

Figure 2. Flow diagram of the study design

[figure not shown]

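### The 10-hour blood contrast cannot separate the first metformin dose from time of day and feeding, yet significant methylation and RNA differences are attributed to the drug

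*Protocol*

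**What the plan says.** Blood for methylation and RNA is taken three times: before the first dose on Day 4, 10 hours after that dose, and on Day 11 (Blood sample collection).

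- **Reference.** At visit 3 the blood "will be collected from the participant's at fasting-state for further genotyping, DNA methylation, RNA expression and metabolite analysis".
- **10-hour sample.** At visit 4 on the same day, before the second dose, "blood samples (7 - 13 ml) from the study participant will be repeatedly collected for DNA methylation, RNA expression and metabolite analysis". No fasting condition is given. In Figure 1 the label reads "Blood samples collected (after 10h", while the Day 4 pre-dose and Day 11 samples are labelled as fasting.
- **Food.** Under Dosage, packaging, storage: "Participants will use the medication during or after eating with a glass of water to reduce the risk of side effects".
- **Attribution.** DNA and RNA analysis states that "metformin-induced changes in the epigenetic gene regulation, DNA methylation and gene expression profiles, will be determined by comparing reference samples" with the later ones. The text under Secondary parameters related to efficacy adds that significant post-dose alterations will confirm the effect of metformin on epigenetic regulation, and it names 10 hours among the three time points.
- **Control.** The study has one arm. Study Design credits self-control with "automatic control of constant influencing factors", such as genotype and gender.

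**The concern.** Self-control removes what stays the same within a person. Clock time and feeding do not stay the same between these two draws, and they change in the same direction in every participant. Any locus or gene that moves with time of day or after a meal would appear in the 10-hour contrast and be read as a metformin effect. Multiplicity control does not help, because such differences can be real without being due to the drug.

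The protocol itself gives reason to take feeding seriously. Its background section on genetic variation and epigenetics says that diet and physical activity are associated with methylation in peripheral tissues, including loci tied to insulin secretion and signalling. Those are loci a metformin study would be inclined to highlight. Secondary objective 2 sets out to separate drug from diet, but only for the gut microbiome.

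At stake is whether ordinary within-day variation is published as a mechanism of metformin.

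**Working it through.** **The plan's own figure.** Study group gives 50 participants, power of at least 80%, alpha 0.05 and about 2% loss. The loss step is consistent: 50 × 0.98 = 49 and 49 / 0.98 = 50. The 80% cannot be reproduced, because no effect size or SD is stated. The check below uses 49 completers and assumes a two-sided test.

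**Can the effects be separated?** Fit one effect per participant (49), a drug effect at 10 hours, a drug effect at Day 11, and an effect of being later in the day and fed.

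| Sample | Drug, 10 h | Drug, Day 11 | Later and fed |
|---|---|---|---|
| Day 4 pre-dose | 0 | 0 | 0 |
| Day 4, 10 h | 1 | 0 | 1 |
| Day 11 | 0 | 1 | 0 |

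The model has 49 + 3 = 52 columns but rank 51, because the first and third effect columns are identical. More participants do not change this. The effects separate only if the 10-hour and Day 11 drug effects are assumed equal (51 columns, rank 51), which the protocol does not assume.

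**How often would a pure time or feeding shift be called a drug effect?** For a paired t-test with n = 49, a shift of δ SDs of the paired difference gives a noncentral t with 48 degrees of freedom and noncentrality δ√49 = 7δ. The critical value is 2.011. With no drug effect:

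| Shift δ (SD of paired difference) | Probability significant |
|---|---|
| 0 | 0.05 |
| 0.1 | 0.11 |
| 0.2 | 0.28 |
| 0.3 | 0.54 |
| 0.4 | 0.78 |
| 0.5 | 0.93 |
| 0.8 | about 1.00 |

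Power reaches 80% at δ = 0.408 (noncentrality 7 × 0.408 = 2.86).

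**Scale.** If within-person errors are equal and independent with SD σ, the paired difference has SD √2·σ. So 0.408 SD of the difference is 0.408 × 1.414 = 0.58 within-person SD. A shift of 0.41 within-person SD is 0.41 / 1.414 = 0.29 SD of the difference and would be flagged only about 51% of the time.

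**Would agreement in direction at Day 11 screen out false attributions?** Both changes subtract the same pre-dose value, so under equal independent errors their correlation is σ² / 2σ² = 0.5. In a simulation with no drug effect (n = 49, 100,000 trials per shift), the share of significant 10-hour changes that also had the same sign at Day 11 fell from 83% at δ = 0.1 to 50% at δ = 0.8. Requiring the Day 11 change to be significant as well, at unadjusted 0.05, cut this to 12% at δ = 0.1 and 2% to 4% for δ from 0.3 to 0.8.

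**The case against.** The strongest reply is that the trial is declared exploratory, its primary endpoint is gut microbiome composition, and only one of two blood contrasts behind secondary endpoint 1 is affected. That stands and limits the weight of the point. It is not trivial, though: methylation and transcriptome profiles are also listed among the primary parameters for efficacy.

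The second reply is that the plan already has adjusters. None of them separates the two effects:

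- The neutrophil/leukocyte ratio is stated for methylation only. Haematology is scheduled only in the verification period, so it cannot track within-day changes in cell mix.
- Plasma metformin should be absent from all pre-dose samples. Variation in level between participants gives partial, model-dependent information at best.
- The diet diary is meant to help identify factors influencing epigenetic profiles, but no analysis is described that uses it to separate meals from drug at 10 hours.
- The listed covariates are biochemical, haematological and anthropometric. Neither clock time nor feeding is among them.

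Some stronger readings are tempting, and the documents do not support them:

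- A reader might infer that thousands of genes would be misattributed. The documents give neither the number of genes tested nor the share that varies with time or meals, so any such count only restates an assumption.
- A reader might infer that the sample is taken in the evening after several meals. No clock times are given. What follows from the text is a gap of at least 10 hours and at least one meal.
- A reader might infer that all blood results fail. The Day 11 sample is fasting and so matched to the reference on feeding, although its clock time is not stated either.

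**Conclusion.** The point holds for the 10-hour contrast in methylation and RNA. The protocol attributes statistically significant changes to metformin, yet in that contrast the drug effect is fully confounded with time of day and feeding, and neither sample size nor the listed adjusters can resolve it.

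With 49 completers and no drug effect, a shift of 0.41 SD of the paired difference would be flagged 80% of the time per locus. This rests on a two-sided unadjusted 0.05 paired t-test. The conversion to 0.58 within-person SD also needs equal, independent errors. A stricter per-locus threshold would require larger shifts, but whatever was flagged would be misattributed in the same way. The actual size of time and feeding effects in these participants is not given, so the number of false attributions cannot be stated.

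The defect lies in a stated rule of inference for a secondary endpoint of an exploratory trial. It does not touch the primary endpoint.

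**What to change.** In DNA and RNA analysis and in the text under Secondary parameters related to efficacy:

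1. Rest claims of metformin-induced change in methylation and RNA, and any claim about blood metabolites, on fasting Day 4 pre-dose versus fasting Day 11.
2. Report 10 hours versus pre-dose descriptively, labelled as first-day change not separable from time of day and meals.
3. Do not use the same direction at Day 11 as evidence of a drug effect. Describe a 10-hour change as consistent with a drug effect only where the Day 11 change at that locus is itself significant after multiplicity control. Treat correlation with plasma metformin as supportive only.
4. Record clock time and time of last meal at each draw.
5. In the same edit, reconcile the visit label: DNA and RNA analysis assigns the end-of-treatment sample to visit 7, whereas the visit schedule draws that blood at visit 6 on Day 11.

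The cost is protocol wording and two recorded times per draw. The scientific price is that a truly transient first-day response can no longer be claimed as a metformin effect. Recovering that claim would need an untreated sample matched on clock time and feeding, which makes the model estimable (52 columns, rank 52) at the cost of further blood sampling for each participant.
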